## Methods and Analysis

### Setting, Participant Recruitment, and Eligibility Criteria

The study will be conducted at the ISIS Centre, a rehabilitation ward of Wakari Hospital (Dunedin, New Zealand), where people with neurological conditions undergo outpatient and inpatient treatment. Participants will be referred by neurologists from the Neurology Department at Dunedin Public Hospital (Southern District Health Board). The ISIS Centre is part of the Southern District Health Board of New Zealand and covers the neurological rehabilitation of 7% of the country's population (~337,000 people).

The inclusion criteria will be:

Aged 18 or olderNew or returning patients presenting to the participating Neurology DepartmentDiagnostic investigations by a neurologist including the appropriate medical examination have been completed.Diagnostic investigations resulted in a diagnosis of FNSD with abnormal movement according to diagnostic criteria of DSM-5 (1) or of a PMD according to the diagnostic criteria by Gupta and Lang (2). Acute (<6 months) as well as persistent symptom presentations (≥6 months) will be accepted.The symptoms cause clinically significant distress or impairment in social, occupational, or other important areas of daily functioning.

Exclusion criteria will be:

Diagnosis of a complex regional pain syndrome, Dissociative Identity Disorder, or Posttraumatic Stress Disorder of high severity with significant dissociationSevere mental health disorder requiring inpatient mental health treatment or potentially affecting trial participation (e.g., suicidality, acute psychosis, active or extensive self-harm)Receiving concomitant psychological intervention that targets motor symptomsInitiation or change in regimen of psychopharmacotherapy at any time between 4 weeks before baseline assessment and the final follow-up assessmentPresence of significant physical trauma/comorbid health conditions (e.g., significant musculoskeletal injuries, severe respiratory illness) precluding participation in our movement retraining (we will include participants who are diagnosed neurological conditions, as long they have individual symptoms that are considered to have a high degree of certainty that they are functional)Low English language proficiencyInability to provide informed consent to participate in the trial

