
### Data and Patients' Safety Monitoring

Participants with any type of neurological diagnosis with a range of associated physical disabilities (e.g., weakness, balance difficulties) are at some risk of falling. According to clinical observations, people with FNSD/PMD are at lower risk of injury than people with neurological damage (16). However, there are still some incidents with this group. Treatment necessarily involves taking managed risks whilst ensuring safety, using management strategies and mobility aids. All trial participants will be assessed by a physiotherapist as they start the movement retraining part of the treatment (see *Interventions*) and throughout the treatment if needed, to ensure adequate steps are taken to ensure safety. In the case of serious adverse events (SAE) the Severity Assessment Code (SAC) rating for adverse event reporting (33) will be completed by the therapist. The study therapist has to contact the principal investigator (MR) within 24 h after the event. The PI will not be blinded to the result of the randomization and will therefore be able to decide if the SAE was a serious adverse reaction to the trial treatment.

In order to monitor and supervise the progress of the trial and SAEs associated with the trial treatment, an independent Data Safety and Monitoring Board will be involved, including a psychiatrist, a statistician, a manager of the ISIS Centre and a person who was formerly treated for FNSD at ISIS as a stakeholder of patients' interests. The DSMB will meet on a regular basis and will make final decisions to terminate the trial prematurely for harm, based on their monitoring and evaluation of SAE attributed to our treatment. The SAC rating for adverse event reporting allows for differentiation of four levels of severity of adverse events (34). In the case of severe and major events (SAC 1 and 2), the trial would have to be suspended with immediate effect pending investigation. The DSMB will discuss SAC 3 and 4 events (minor to moderate events), how they relate to our treatment and how they will influence the further course of this trial. The DSMB will also make final decisions to terminate the trial prematurely for benefit, based on stopping rules and interim analyses described below (see *Sample size, power calculations, and interim analyses*).

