Besides the strengths, we anticipate several limitations. We have already discussed risks of bias and have implemented tools to reduce these risks. There are additional challenges that we anticipate with implementing the study procedure. First, recruiting from one hospital can limit the representativeness of our sample and can hamper the potential to gain the optimal sample size. The institution where we will conduct our trial covers the neurological rehabilitation of a substantial part of the NZ population, which will ensure our sample is largely representative for the region. We first want to ensure the feasibility of our trial at this site before considering the potential to extend the trial to at least one other site. With a priori planned interim analyses, we will regularly check if the conservative estimation of our optimal sample size will need correction. Second, the design of our active control intervention has several advantages mentioned above. Nonetheless, we have to expect indirect therapeutic effects of our active control treatment (e.g., incidental change in beliefs after re-establishing a normal movement). Even accounting for the active control treatment being potentially less effective than NH-CBT, it seems likely that the mean difference between groups will be small. Our power analysis therefore builds on a conservatively estimated small between-group effect. When designing the control intervention, we also had to consider the pragmatic fact that a treatment-as-usual or a waitlist control group would not have been feasible, because our institution is the only one covering neurorehabilitation for patients from a bigger district in New Zealand, implying limited resources and long waitlists for receiving treatment. Third, another pragmatic limitation is that we have to accept participants in the inpatient and outpatient settings as well as participants of older ages. We will apply statistical strategies to control for the type of treatment setting in our data analysis. We will include older participants only if motor symptoms are considered highly likely to be functional and not related to age-related degenerative processes. Fourth, our 8-week follow-up window after the end of treatment is very short. Again, due to pragmatic reasons associated with delivering both treatments in the context of a clinical service, we would not be able to let our control participants wait for a longer period than this before they receive NH-CBT. At the same time, we consider the *controlled* follow-up assessment as an important strength of our study design. Finally, we will implement several methods to ensure treatment fidelity (e.g., frequent supervision, audio-recording the initial therapy session, and feedback to therapists). However, we will not be able to completely exclude the risk of therapists deviating from our rules of treatment fidelity and exposing participants to distraction techniques or interventions that address illness beliefs.

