
NH-CBT is a strongly theory-driven treatment concept, combining the two first-line interventional approaches for FNSD/PMD in a unique way. Its interdisciplinary character, involving neurologists, clinical psychologists, physiotherapists, occupational therapists, and other rehabilitation professionals is in accordance with a biopsychosocial understanding of persistent physical symptoms. This stands in contrast to a more reductionistic biomedical model and arguably better addresses the multidimensional etiopathogenesis of a complex phenomenon such as functional motor symptoms. We see much potential to improve the treatment outcome for patients with complex conditions such as FNSD in formulating links between different disciplines into a coherent, theory-driven, truly interdisciplinary approach. Results from previous research focusing on monodisciplinary approaches have not been convincing. For example, a recently published RCT showed no effect of a sophisticated CBT treatment for patients with functional epileptic seizures on the frequency and severity of seizures and mostly small effects on secondary outcomes compared with a treatment as usual (59).

First results from a case series examining the effects of NH-CBT show promising effects (27). The sensible next step is to investigate the efficacy of NH-CBT in a randomized trial and to gain knowledge about how well the intervention's effect can be sustained and by which variables it is moderated. If demonstrated to have efficacy, we would then prioritize an evaluation of its effectiveness and feasibility nationally and internationally, with the aim of implementing NH-CBT into routine practice worldwide. We anticipate challenges associated with implementing an interdisciplinary treatment that requires a whole team to be committed to a mutual therapeutic understanding. However, the experience at the rehabilitation center where NH-CBT originated has been that this was not a considerable impediment in the context of an existing interdisciplinary approach to neurorehabilitation. Countries such as New Zealand and Australia are often progressive in implementing treatment for chronic conditions in interdisciplinary treatment settings, e.g., the National Pain Strategy in Australia (60). A successful trial has the capacity to transform the lives of individuals living with functional neurological symptoms and substantially reduce financial burdens on healthcare systems around the world.

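### The monitoring board is called independent, yet one seat goes to a manager of the only current trial site, with no stated limit on that member's access to by-arm interim results

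*Protocol article*

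**What the plan says.** The composition and powers of the board are set out under Data and Patients' Safety Monitoring: "an independent Data Safety and Monitoring Board will be involved, including a psychiatrist, a statistician, a manager of the ISIS Centre", and a person formerly treated there who speaks for patients. The same section lets the board decide finally on ending the trial for harm, from its own evaluation of serious adverse events attributed to the treatment. On efficacy it adds: "The DSMB will also make final decisions to terminate the trial prematurely for benefit, based on stopping rules and interim analyses described below".

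Those analyses are defined under Sample Size, Power Calculations, and Interim Analyses. Eight are allowed, and Table 3 gives a sample size and a p-value for each. The person who conducts them must be separate from the daily running of the trial. Nothing comparable is said of the people who receive the results and decide.

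On the site, the section on setting and recruitment states: "The study will be conducted at the ISIS Centre, a rehabilitation ward of Wakari Hospital". The Discussion confirms that this is one site for now: "We first want to ensure the feasibility of our trial at this site before considering the potential to extend the trial".

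**The concern.** A monitoring board is called independent so that those who see accumulating comparative data, and decide on stopping, have no part in running the trial or delivering its treatments. A manager of the sole site does not meet that description. The article states both the label and the seat, so this is a conflict within the text and not a detail left to a charter.

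Two things are at stake:

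- **Confidentiality of interim trends.** The manager belongs to the centre where the unmasked investigator and therapists work. A trend that became known there could colour eligibility judgements, delivery of therapy or encouragement. The primary outcome is a self-reported scale, which blinded assessors do not protect.
- **Credibility of a stopping decision.** If the trial stops early, or is continued after a safety discussion, readers will ask who decided. The investigator delivers the NH-CBT education session and also decides whether a serious event was a reaction to treatment. The board is the only oversight body that the article places above the investigator, so its independence carries weight.

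**Working it through.** The point is about composition, so the check is to set the provisions side by side.

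1. **Is the member tied to the site?** Yes. The safety section names a manager of the ISIS Centre, and the setting section names that centre as the place where the trial is run. The Discussion treats a second site only as a later possibility.

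2. **Does the board act on comparative results?** Yes, by implication. Stopping for benefit rests on the interim analyses. Table 3 attaches a p-value that requires a stop to each look. In a two-arm superiority trial, such a test of benefit compares the arms.

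3. **How often?** Table 3 lists looks at 22, 44, 66, 88, 110, 133, 155 and 172 participants. The last is the full planned sample, so 8 − 1 = 7 looks come before the final one.

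4. **How much judgement is involved?**
   - *Benefit:* little. The thresholds are fixed in advance, from 0.00000003 at the first look to 0.036 at the seventh.
   - *Harm:* more. Events in Severity Assessment Code classes 1 and 2 suspend the trial at once pending investigation. Classes 3 and 4 go to board discussion. Termination for harm is left to the board's evaluation, with no numerical rule.

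5. **Does another provision restore independence?** The only one concerns the person who conducts the interim analyses. The article describes no closed session, recusal or non-voting role for the manager.

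6. **Who at the centre could be affected by a leaked trend?** Methods for Minimizing Bias says that the investigator and the therapists are not masked. Study Design and Procedure places eligibility and consent in the interview held by the investigator. Table 1 assigns the NH-CBT education session to the same person.

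The design figures are not affected. The planned total of 164 before dropout is reproduced by the repeated-measures interaction formula, with noncentrality N·m·f²/(1 − r) = 164 × 3 × 0.10²/(1 − 0.5) = 9.84, which gives power 0.805 on 2 and 324 degrees of freedom. The finding rests on no figure beyond the count of looks.

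**The case against.** The case on the other side is substantial, and much of it stands.

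- **Access is not described.** The article does not say what each member receives. The board might be told only whether a boundary was crossed, and a charter that is not shown might keep the manager out of closed sessions. So a reader may infer that the manager sees and votes on the accumulating effect, but the text does not say so. What remains is that the article claims independence for the whole board while listing a seat that lacks it.
- **Safeguards exist.** The efficacy thresholds are pre-specified, someone outside the daily running of the trial does the analyses, and the gravest events bring automatic suspension, which the manager cannot block. These narrow the scope for influence. They neither stop knowledge of a trend from entering the centre nor govern the final decision on harm.
- **Some routes to bias are weak.** Referrals come from hospital neurologists, not from centre staff. Allocation was prepared by an unaffiliated associate and is held in sealed opaque envelopes, so a known trend does not reveal the next assignment. NH-CBT therapists are already told to convey optimism and control therapists are not; that asymmetry exists without any leak.

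Stronger readings are also tempting and are not supported:

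- That the manager runs the service that developed NH-CBT. The text says only that the member is a manager, and the Discussion speaks of "the experience at the rehabilitation center where NH-CBT originated" without naming it. ISIS is the natural reading, but an inference.
- That the manager has an interest in how long the trial lasts. The remark "implying limited resources and long waitlists for receiving treatment" explains why a usual-care or waitlist control was not feasible. It says nothing about a manager's stake.
- That half the board is compromised (2 of 4). The list of members need not be exhaustive, and a former patient who represents patients' interests is a legitimate member. The article does not say which treatment that person received.
- That exposure starts at 13% of enrolment (22/172 = 12.8%). The article does not say whether a look counts participants enrolled or participants with outcome data.

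**Conclusion.** The concern holds for one seat. The board is described as independent, but a manager of the only current site sits on it. It has the final decision on stopping for harm and for benefit, with up to seven comparative looks before the final one, and the article states no limit on that member's access or role.

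The size of any resulting bias cannot be calculated from the document, and none is shown to have occurred. The consequence is a risk to the confidentiality of interim results and to the credibility of an early stop. The conclusion assumes that board members ordinarily receive what the board decides on. If a charter already excludes the manager from by-arm data and stopping decisions, the defect shrinks to wording that one sentence in the protocol would correct. It should be corrected, because the remedy is cheap and a stopping decision is hard to defend afterwards.

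**What to change.** State in the protocol and the board's charter that by-arm interim results, by-arm safety data and decisions to stop or continue are reserved for members with no management or staff role at the ISIS Centre. Then choose one of two arrangements for the manager's seat:

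- the ISIS manager attends open sessions only, with recruitment and safety information pooled across arms; or
- the seat goes to a rehabilitation manager or clinician from outside the centre.

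The patient representative can stay as a full member.

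The cost is a change of wording and perhaps one replaced seat. The closed sessions lose some local operational knowledge, part of which the manager can still supply in the open session. The sample size, Table 3 and the analysis model need no change on this account.

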### Interventions

#### Structure, Providers, and Treatment Fidelity

Participants in both study groups will first receive an explanation of their functional motor symptoms by their neurologist, as part of the *neurological assessment* (described earlier under *Study Design and Procedure*). The main part of the intervention in both groups will start with an initial 60–90 min session that includes education of participants. In both groups, this initial session will be followed by a minimum of 2 up to a maximum of 23 sessions of movement retraining and one final session of relapse prevention. Differences between the groups in the content of the initial session, the movement retraining and the relapse prevention are described below. Sessions will last between 30 and 120 min and will be delivered face to face over 8 weeks. The frequency and scheduling will depend on participants' individual needs (e.g., type and severity of symptoms) and stamina. (see Criteria for finishing the movement retraining before a maximum of 23 sessions can be found in Table 1 under “8. When and how much”. Sessions will follow a treatment manual and will take place either as an inpatient or an outpatient treatment. For both interventions, the initial education session will be conducted by a licensed clinical psychologist, and the movement retraining will be delivered by a licensed rehabilitation professional (physiotherapist, occupational therapist, rehabilitation assistant), but will necessarily involve physiotherapist oversight and involvement at some point. Gender, age, professional backgrounds, and years of experiences of the neurologists, clinical psychologists, and rehabilitation professionals delivering the NH-CBT and the control intervention will be recorded in the main trial paper. Table 1 outlines details of Nocebo-Hypothesis Cognitive Behavioral Therapy (NH-CBT) and the active control treatment (supportive counseling and movement retraining), as well as the means of ensuring treatment fidelity, according to the TIDieR checklist (37).

**Table 1 T1:** Nocebo-Hypothesis Cognitive Behavioral Therapy and supportive counseling and movement retraining (active control intervention) described following the TIDieR checklist.

**Items TIDieR checklist**		
1. Name	Nocebo-Hypothesis Cognitive Behavioral Therapy (NH-CBT)	Supportive counseling and movement retraining
2. Why	The current intervention is based on a predictive coding theory of FNSD/PMD. This theory highlights the following key mechanisms of functional motor symptoms: Pre-disposing factors (e.g., past events experienced or witnessed that lead the person to doubt the integrity of their neurological system) lead to a mental representation of their body/parts of their body to be neurologically damaged or vulnerable to neurological damage, dysfunction or disease. When triggered by a specific situation (e.g., that strongly confirms that belief), neurological functioning starts to change creating physical symptoms.	The control intervention is designed to control for the non-specific effects of (a) education about symptoms, (b) emotional support from a therapist, and (c) movement retraining. The intervention is based on a model of sequential motor learning (16). This model assumes that movement can be retrained or “reprogrammed” by utilizing a sequential approach to re-establish more normal movement patterns.
3. What (materials)	*Information for Neurologists:* Neurologists will receive written information about a standardized explanation of FNSD/PMD, following suggestions by Stone (29) (emphasizing the mechanism of the symptom rather the cause, explaining how the diagnosis was made, emphasizing that it is common, emphasizing reversibility, that self-help is essential for recovery, the possible effect of depression and anxiety on symptoms, and the use of metaphors).	
	*Worksheet*: Written information about the diagnosis and treatment will be provided to participants in the initial educational intervention, to supplement the verbal explanations. This sheet will outline the “nocebo hypothesis” regarding functional symptoms, including information about the concept of subconscious processing and the placebo/nocebo effect, as well as affirming much of the information given by the neurologists. The description of the treatment will deliver more information about the movement retraining, including video feedback.	*Worksheet*: Written information about the diagnosis and treatment will be provided to participants in the initial educational intervention, to supplement the verbal explanations. This sheet will contain information similar to that outlined by the neurologists (see TIDieR Checklist item 3), as well as the basic information about the physical therapy component of the treatment program.
	*Intervention manual*: Each therapist in the experimental condition will receive a NH-CBT manual that complements the NH-CBT training and contains background information about FNSD/PMD, a guide to using the treatment manual, and a detailed description of each of the treatment components with examples of wording.	*Intervention manual*: Each therapist in the control condition will receive a manual describing the supportive counseling and movement retraining, containing a guide to using the treatment manual, a detailed description of each of the treatment components with examples of wording, and information about what content should be avoided (e.g., explaining the nocebo effect and the role of beliefs as mechanisms of the symptoms).
	Portable electromyography biofeedback unit and tablet to provide video feedback	Since the control intervention does not include video feedback or any other form of visual feedback, no tablet or electromyography biofeedback unit is provided.
	Additional materials such as mobility aids (e.g., walking frame), parallel bars, treadmill, etc. may be required depending on the participant's needs	
4. What (procedures)	*Neurological assessment*: Participants in both study groups will be assessed by a neurologist prior to be enrolled in the trial. The neurologists will provide the participant with a standardized explanation of FNSD/PMD (see TIDieR Checklist item 3).	
	*NH-CBT psychoeducation (1 session)*: *Understanding the diagnostic evidence*: Therapists are asked to study participants' health records to gain objective evidence for the FNSD/PMD diagnosis and to identify any historical reasons why someone might believe that they are susceptible to the symptoms they are presenting with (including past medical events, the onset, and course of symptoms). *Assessment:* The main goal of this part of NH-CBT is to explore pre-disposing factors and triggers of functional motor symptoms from participants' subjective point of view. *Transparent sharing of the nocebo hypothesis:* This treatment component addresses participants' personal beliefs about the causes of their symptoms, and their understanding of the terms “subconscious” and “placebo/nocebo effect” (using a graphical aid and metaphors to explain the effect of expectations and belief that a medication works) is explored. A psychological formulation is shared with the participants that incorporates presenting motor symptoms within a hypothesis that symptoms are due to a “nocebo effect.” The aim is to engender in the participant an alternative belief about their symptoms, to challenge the one currently held. The therapist rounds up this component with framing the role and goals of the movement retraining within the nocebo hypothesis.	*Psychological input and supportive counseling (1 session)*: The first session of the active control intervention includes elements of a treatment protocol by Nielsen et al. (30). *Assessment:* The participant's symptom history is assessed regarding current symptoms and health-related problems, symptom onset, predisposing/precipitating/perpetuating factors, symptoms' impact on daily life, previous experiences with treatments and health care professionals, and exploration of participants' understanding of their symptoms and their cause. *Education:* The therapist reiterates the education about FNSD/PMD that was given earlier by the diagnosing neurologist according to the suggestions by Stone (29). The therapist will ensure that the person knows that symptoms are not caused by structural damage or a degenerative process. Then a brief symptom model of FNSD/PMD is provided that conceptualizes functional motor symptoms as a result of a fight or flight (survival) response and secondary behavioral changes (e.g., avoidance behaviors) causing disability. *Supportive counseling*: The therapist uses active listening and supportive counseling skills (e.g., conversation about coping strategies, impact of symptoms on family, and work) but should not adopt a structured therapy approach.
	*NH-CBT movement retraining with video feedback (2–23 sessions)*: The participant is then given opportunities to physically experience themselves as functioning better. The movement retraining is individualized, according to participants' symptoms and needs. The intervention manual proposes exercises for different forms of functional motor symptoms (e.g., functional weakness, balance, tremor, abnormal gait/jerks/myoclonus/involuntary movements, or fixed dystonia). The exercises function as behavioral experiments, to demonstrate to participants that their brains and bodies are capable of working better/normally under certain circumstances. This variability is interpreted to be almost always a sign that there is no damage or disease causing the symptoms. Therapist and participants repeatedly reflect that any improvements can only be due to a change of belief, thus strongly suggesting that belief is the mechanism behind the symptoms. *Distraction:* Distraction, or varying participants' attention to other stimuli, is an important principle of the NH-CBT movement retraining and is almost always the way to create this momentarily improved functioning. A distractor is previously selected collaboratively by therapist and participant (e.g., their favorite music) and is presented whilst participants engage in relevant physical movement. *Video recording/feedback*: Another important element of the NH-CBT movement retraining is video recording and immediate video feedback if the participant shows improved movement when distracted. Improved functioning seen on video feedback is framed as evidence that the “nocebo hypothesis” is valid: symptoms are not caused by structural neurological damage and their bodies are more capable than participants previously believed. More physical activity is then attempted, with further video feedback, and this treatment cycle is repeated, attempting more, and more complex activity as the participant improves. *Purposeful optimism:* Throughout treatment, therapists will be specifically instructed to portray as much optimism as possible to the participant about potential recovery, e.g., talking about how many people have got better using this treatment.	*Control movement retraining (2–23 sessions)*: The movement retraining part of the control intervention is based on a sequential motor learning approach proposed by a consensus recommendation for physiotherapy for functional motor disorders (16). The main rationale for movement retraining is that FNSD/PMD can be conceived of as unwanted patterns of movement that have been subconsciously programmed and learned, and are outside the person's control. It is assumed that these patterns cause symptoms and that symptoms are perpetuated by secondary changes. Movement can be retrained/“reprogrammed” by utilizing a sequential approach to re-establishing more normal movement patterns. *Assessment:* The assessment includes determining levels of falls risk, methods of keeping the person safe, observation of the impact of symptoms on posture and movement, exploring the nature of symptoms, evaluation of any potential compensatory strategies, and exploring possible secondary physical changes. *Sequential approach to restore normal movement patterns*: Elementary symptom free components of movement are established, and built on in successive stages to gradually reshape normal movement patterns. Another target is to change maladaptive compensatory habitual postures, movement patterns, and behaviors. Finally, secondary changes (e.g., physical changes such as deconditioning or changes of social/occupational roles) are addressed. Different movement retraining strategies are provided for different forms of functional motor symptoms in the treatment manual. Therapists are asked to avoid mentioning concepts such as nocebo/placebo effects, beliefs, or expectations. No visual feedback (neither video nor mirror feedback) is used. External distractors (e.g., music, irrelevant conversation) to vary participants' attention are not allowed. Purposeful optimism should not be part of therapists' approach.
	*NH-CBT relapse prevention (1 session)*: The treatment cycle is taken as far as possible in the final session. Therapist and participant collaboratively set a final movement goal that is as high as the participant wishes. The participant then tries to achieve it. The second part of the relapse prevention stage gives clear advice to people about what to do if symptoms re-emerge in future. For each individual person, a personalized behavioral experiment is devised that will prove to participants that their most feared neurological event is not happening. This experiment involves them reminding themselves that minor transient symptom, often referred to as “glitches”, are harmless and are just the subconscious expressing a momentary doubt via a nocebo effect.	*Control relapse prevention (1 session)*A self-management plan is introduced to the participant, including a summary of useful strategies that help to normalize movement, activity plans to address boom and bust patterns and how to progress activity, future goals, and what to do on difficult days and during periods of symptom exacerbation. Therapists are instructed to avoid making any suggestions that state or imply the role of illness beliefs.
5. Who provided	*Neurological assessment:* All neurologists involved in this trial will be employed on consultant level. They will receive training from the PI (MR) in person or by telephone. They will have been given suggestions by Stone (29) of how to explain FNSD/PMD to participants.	
	*NH-CBT psychoeducation*: clinical psychologist (PI: MR)	*Psychological input and supportive counseling*: clinical psychologist (other than PI)
	*NH-CBT movement retraining*: licensed rehabilitation professional (physiotherapist, occupational therapist, rehabilitation assistant), with a physiotherapist always having a role in developing the treatment plan (including safety management plan) and having oversight of the physical elements of the treatment	*Control movement retraining*: licensed rehabilitation professional (physiotherapist, occupational therapist, rehabilitation assistant), with a physiotherapist always having a role in developing the treatment plan (including safety management plan) and having oversight of the physical elements of the treatment
	Multi-disciplinary staff members delivering the initial educational or movement retraining intervention will have received training from the principal investigator (MR) which can take between 0.5 and 1 day (depending on the professional's level of experience). Each staff member will be trained either in NH-CBT or in the control intervention. We will use a brief checklist to ensure that the rehabilitation professional has demonstrated an understanding or proficiency in delivering the key ingredients of the intervention. All staff members involved in this trial will receive a comprehensive treatment manual. All professionals who deliver treatment within this trial are required to attend supervision frequently with a licensed supervisor experienced in CBT for individuals with functional neurological symptoms. The initial therapy session will be recorded. The supervisor will give immediate feedback to the therapists (of the control group in particular) in case they would expose participants to distraction techniques or interventions that address illness beliefs. At least one supervision session will be planned for every intervention participant treated.	
6. How	All sessions will be delivered as individual sessions in a face-to-face format as part of either an inpatient or outpatient treatment.	
7. Where	The majority of sessions will occur at the ISIS (Rehabilitation) Centre, Wakari Hospital, Dunedin, for both inpatient and outpatient treatment, although some sessions will occur in community settings for some participants, predominantly when they are in the latter stages of treatment.	
8. When and how much	1 neurology session (30–50 min) 1 initial session of education (60–90 min) Minimum 2 up to maximum 23 NH-CBT or control movement retraining sessions (30–120 min) over 8 weeks 1 session of relapse prevention (30 min) Participants can stop therapy before the 25 h limit if they (a) subjectively consider themselves to be fully recovered, (b) can mobilize at 5.0 km/h on a treadmill for 15 s, and (c) had at least one initial psychoeducation session and 2 sessions of movement retraining. These criteria are consistent with the suggestion by an international Functional Neurological Disorders Core Outcome Measure Group (35).	
9. Tailoring	The intervention is standardized by a treatment manual. The manual describes opportunities of how the education at the beginning can be tailored according to participants' individual functional motor symptoms and problems. The movement retraining session tasks and training will be adapted according to participants' individual symptoms. However the rehabilitation professionals are encouraged to focus on the key principles of the treatment.	
11. How well (planned)	All therapists in this trial must adhere to a therapy manual and receive training in the treatment content and procedure. Therapists are required to attend supervision frequently with a licensed supervisor experienced in CBT for individuals with functional neurological symptoms. Treatment fidelity will be assessed as follows: All initial therapy sessions will be audio-recorded. A checklist of key treatment objectives and principles will be used to assess treatment fidelity and its two components, therapist adherence and treatment specificity, for both the NH-CBT and the active control intervention. We will assess therapist competence with a validated rating scale [e.g., Cognitive Therapy Scale (36)]. Session records of a randomly selected sample (30% of the intention-to-treat sample) will be rated by two independent, blinded raters.	

*Item 10 (Modifications: If the intervention was modified during the course of the study, describe the changes) and 12 (How well [actual]: If intervention adherence or fidelity was assessed, describe the extent to which the intervention was delivered as planned) of the TIDieR Checklist do not apply to our trial and are omitted from this table*.

